### Recruitment

2.9

Participant recruitment will be conducted at the Faculty of Sports Sciences at Ferdowsi University of Mashhad in Mashhad, Iran. The selection of participants will adhere to specified inclusion and exclusion criteria.

### Eligibility

2.10

Individuals expressing interest in participation will undergo an assessment to determine their eligibility based on the established criteria. Eligible participants will be provided with a consent form to complete.

### Consent Process

2.11

Informed consent will be obtained by the principal investigator or trained staff during the initial screening visit. Participants will receive verbal and written explanations of the study, risks, and benefits, with time for questions. Consent forms will be signed in duplicate, with one copy provided to the participant.

### Confidentiality

2.12

Participant data will be anonymized using unique codes. Personal information will be stored separately from study data and accessible only to the research team. All procedures will comply with the Declaration of Helsinki and local privacy laws.

### Allocation: Sequence Generation, Concealment, and Implementation

2.13

This double‐blind, placebo‐controlled, crossover study will randomize 28 semi‐professional wrestlers to receive either beetroot juice enriched with 90 mg vitamin C (8.4 mmol nitrate) or a placebo drink (240 mL each) in random order, with a 14‐day washout period to eliminate carryover effects. Randomization will be performed using a web‐based tool, with allocation details concealed in consecutively numbered opaque envelopes managed by an independent staff member.

Blinding will be maintained for participants, assessors (care providers), and investigators. The intervention and placebo drinks will be visually identical. Drinks will be prepared and labeled with participant numbers by the independent staff member, ensuring that participants and assessors (conducting Wingate tests, blood sampling, and RPE questionnaires) remain unaware of group allocations. Investigators overseeing the study will have no access to allocation details until data collection is completed. Data will be coded with participant numbers to maintain unbiased analysis.

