### Data Collection Methods

2.17

Data will be collected using standardized forms and electronic records. Wingate test data will be recorded directly from the Monark ergometer software. Blood samples will be analyzed in a certified laboratory using automated analyzers for CK, LDH, and glucose. RPE will be assessed via the Borg scale immediately post‐test. A 72‐h food recall will be administered by trained staff to verify dietary adherence. All data will be double‐entered to minimize errors.

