### Statistical Analysis

2.21

Data will be analyzed using SPSS v26. Normality will be assessed via the Shapiro‐Wilk test. Comparison of the within‐subject effects of BRJ (90 mg vitamin C) versus placebo will be evaluated using paired t‐tests (for normal data) or Wilcoxon signed‐rank tests (for non‐normal data). A univariate General Linear Model (GLM) will be used to assess treatment, sequence, and treatment‐sequence (carryover) effects. Statistical significance will be set at *p* < 0.05.

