### Data Management

2.22

Data will be stored securely on password‐protected servers at Mashhad University of Medical Sciences, with access limited to authorized investigators. Participant identifiers will be coded to ensure confidentiality. Quality checks will include range validation and consistency audits. Data backups will occur daily, and the database will comply with local data protection regulations.

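### Release of the allocation is tied only to the end of data collection, so it may precede data checks and analysis, and coding by participant number does not mask treatment once the list is open

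*Protocol article*

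**What the plan says.** Section 2.13 (Allocation) of the protocol article names who is blinded: "Blinding will be maintained for participants, assessors (care providers), and investigators". It gives one time limit on the investigators' access: "Investigators overseeing the study will have no access to allocation details until data collection is completed". The next sentence gives the safeguard for the analysis: "Data will be coded with participant numbers to maintain unbiased analysis". The same section describes how the drinks are identified: "Drinks will be prepared and labeled with participant numbers by the independent staff member".

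Section 2.22 (Data Management) describes the stored data "with access limited to authorized investigators" and lists the checks: "Quality checks will include range validation and consistency audits". It does not say whether these checks come before or after the allocation is released.

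Section 2.17 (Data Collection Methods) has Wingate results taken straight from the ergometer software and blood markers measured on automated analyzers. Trained staff take a 72-hour food recall to verify adherence to the diet.

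**The concern.** The blind has two jobs. During the sessions it protects conduct and measurement. Afterwards it protects every decision taken on the data before the result is known. Section 2.13 covers the first job. For the second it relies on a numeric code that stops masking treatment once the list is open.

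Three kinds of decision may still be open when data collection ends:

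- **Queries and exclusions.** These are values flagged by the range or consistency checks, and sessions found to be invalid or non-adherent.
- **Which result is primary.** Section 2.6 names maximum power in a two-stage Wingate test. The test has an upper-body and a lower-body stage, and the article does not say which stage, or what combination, carries the primary outcome.
- **Which analysis is reported.** Section 2.21 gives a paired test for the drink comparison and also a general linear model that assesses treatment.

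With at most 28 within-person differences, a few such decisions taken with treatment known could shift the result or affect which result is emphasised. At stake is whether the claim of an unbiased analysis rests on the procedure or on the restraint of the people involved.

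**Working it through.** The plan gives no figure to reproduce on this point. The check sets its statements side by side, and a short illustration of size follows.

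**Does participant-number coding mask treatment?**

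1. The data carry a participant number (section 2.13).
2. The drinks carry the same participant number (section 2.13), so the allocation is keyed to it.
3. Each participant has two sessions and one of two orders (sections 2.2 and 2.13.1). Knowing the order gives the treatment in both sessions.
4. It follows that data plus list give the treatment for every record. The number hides a person's identity. It hides treatment only while the list is withheld.
5. Withholding the list is guaranteed only until data collection is complete (section 2.13). The analysis comes after that point.
6. The data are open to authorized investigators (section 2.22), and investigators are the group to whom the time limit applies. The same people may therefore hold both data and list.

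Comparing the drinks also needs a treatment label for each session, which a participant number alone does not supply. Either the true list or a masked code has to be joined to the data. The coding that the article describes is not such a masked code.

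**Must release precede the checks?** No. The limit is an earliest time. The checks in section 2.22 have no stated timing. The text permits release before the checks and equally permits release after them.

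**How much could one decision matter? (illustration on assumed values)**

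Assume that one participant's difference lies z standard deviations from the mean of all n differences and that this participant is excluded. The values z = 1, 2 and 3 are assumptions and come from nowhere in the documents. The n are the planned 28 and the calculated requirement of 22 (section 2.8). The SD is held fixed.

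- Shift of the mean = z/(n − 1), in SD of the differences.
- Standard error = 1/√n: 1/√28 = 0.189 and 1/√22 = 0.213.

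| z (assumed) | n = 28: shift | in SE | n = 22: shift | in SE |
|---|---|---|---|---|
| 1 | 1/27 = 0.037 | 0.20 | 1/21 = 0.048 | 0.22 |
| 2 | 2/27 = 0.074 | 0.39 | 2/21 = 0.095 | 0.45 |
| 3 | 3/27 = 0.111 | 0.59 | 3/21 = 0.143 | 0.67 |

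If the value is instead corrected to the mean, the shift is z/n, which is slightly smaller: 3/28 = 0.107 and 3/22 = 0.136 at z = 3.

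The upper end is uncommon. Under normality about 28 × 0.0027 = 0.076 values beyond 3 SD are expected among 28, so roughly 7% of such trials would contain one. The table shows what one exclusion can do. It does not show how likely an unblinded exclusion is.

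**The case against.** The strongest reply is that the article states no fault in timing. A reader might infer that investigators receive the list as soon as the last sample is drawn, and that checks and analysis follow unblinded. The documents do not support that. Section 2.13 sets an earliest time and does not equate the end of data collection with the last blood draw. Double entry is described under Data Collection Methods ("All data will be double‐entered to minimize errors"), so it may well be finished by then. This objection stands, and the point is limited to what the rule allows.

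A second reply concerns the choice of test. A reader might count the normality check ("Normality will be assessed via the Shapiro‐Wilk test") as a choice exposed to unblinding. It is not. The rule is stated in advance, and on within-person differences the Shapiro-Wilk result is the same whichever drink is subtracted from the other.

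Third, the room for discretion is small. The primary outcome comes from software and the blood markers from automated analyzers. Section 2.3 places confirmation of adherence at arrival, before the drink is given. This stands as a reason to expect a modest effect. It does not settle what happens to a session that is questioned later, and it does not touch the choices about the Wingate stage or about paired test versus linear model.

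Fourth, a database lock, a masked code or a blinded analyst may be set out in a full protocol or SAP that is not shown. That is right, and their absence from a condensed article is not held against it. The point rests on two sentences that are printed: a release condition, and a safeguard that cannot work once that condition has been met. If a fuller document holds a stricter rule, section 2.13 should be brought into line with it.

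**Conclusion.** The point holds in a limited form. Release of the allocation is conditioned only on the end of data collection, so it may precede the range and consistency checks, decisions on invalid or non-adherent sessions, and the analysis. Coding by participant number does not mask treatment from anyone who also holds the allocation list, and so does not by itself secure the unbiased analysis claimed for it.

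The likely impact is modest. The range of 0.2 to 0.7 standard errors for one excluded participant is conditional on an assumed deviation of 1 to 3 SD, and is not an estimate of bias in this trial. The conclusion assumes that the allocation list is indexed by the participant number on the drinks, and that some investigators with data access take part in checking or analysis. The article does not name who performs the analysis.

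This is a weakness that should be corrected, not one that undermines the design.

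**What to change.** In section 2.13, replace the release condition with a rule of this kind: the independent staff member releases the allocation only after the data checks and all decisions on invalid or non-adherent sessions are complete and the database is locked. The primary analysis is then run with drinks coded X and Y, and the code is opened once that result is recorded. The sentence on participant numbers can stay as a statement about confidentiality, but should no longer be offered as the safeguard for the analysis.

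An X/Y code hides the direction of the effect but not its size or p-value. The Wingate stage that carries the primary outcome, and the choice between paired test and linear model, should therefore also be fixed before lock.

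The cost is small. The staff member who already holds the list keeps it a little longer and supplies a masked list that gives X or Y for each participant and session. Version 1.0 states that recruitment had not begun (section 2.1), so on that timetable the change can be made before any data exist.

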#### Sequence Generation

2.13.1

Randomization will be performed using a web‐based tool to generate a balanced crossover sequence (1:1 allocation to start with beetroot or placebo).

#### Concealment Mechanism

2.13.2

Allocation details will be concealed in consecutively numbered opaque envelopes prepared by an independent staff member not involved in assessments.

#### Implementation

2.13.3

The independent staff member will generate the sequence, enroll participants after eligibility screening, and assign interventions by providing the pre‐labeled drinks.

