### Control Group

2.5

Participants assigned to the control group will receive a beverage that visually resembles the beetroot supplement. The placebo drink will consist of a neutral solution containing 0.4 mg/mL citric acid, 0.2 mg/mL food coloring, and 0.25 g/mL sugar, formulated to match the appearance, taste, and texture of the beetroot juice without containing nitrates, vitamin C, or polyphenols.

The beetroot juice intervention will be similarly supplemented with 0.25 g/mL sugar to ensure identical sweetness and caloric content, maintaining effective blinding. Both drinks (240 mL each) will be prepared by a third‐party supplier to ensure consistency and double‐blinding.

After a 3‐h interval, a baseline blood sample will be collected from the subjects. The Wingate upper body functional test will be performed immediately thereafter, followed by the Wingate lower body test, which will be conducted 1 to 4 min later. Blood samples will be collected immediately after the Wingate lower body test and again 24 h later. Additionally, participants will complete the RPE questionnaire during both test sessions.

Given that the half‐life of nitrate is approximately 5 to 8 h, a 14‐day washout period is considered sufficient to effectively reduce any residual effects that may arise from prior nitrate supplementation [35]. Since participants will serve as their own controls, sessions will be scheduled at the same time each day to maintain consistency.

The study's design is illustrated in Figure 3. Throughout the experimental phase, each participant will complete two visits to the laboratory.

Studies have also demonstrated that the performance of high‐intensity lower body exercises is not significantly compromised by prior upper body activity. As such, it will be feasible to conduct lower body testing and training either preceding or following upper body sessions without negatively affecting the power output of the lower body [36]. In this study, we will administer the upper body Wingate test, followed by the lower body Wingate test. This sequential testing design will enable a thorough assessment of the effects of the two supplements on performance across different muscle groups.

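### The staff member who generates and holds the allocation list also enrols the wrestlers and provides the drinks, so allocation is not concealed from the enroller and dosing is probably not blind

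*Protocol article*

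**What the plan says.** The procedure is spread over four places in the protocol article.

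- Section 2.13.3 (Implementation): "The independent staff member will generate the sequence, enroll participants after eligibility screening, and assign interventions by providing the pre‐labeled drinks".
- Section 2.13 (Allocation) places the allocation details in "consecutively numbered opaque envelopes managed by an independent staff member" and adds: "Drinks will be prepared and labeled with participant numbers by the independent staff member".
- Section 2.13.2 (Concealment Mechanism) says that the details are "concealed in consecutively numbered opaque envelopes prepared by an independent staff member not involved in assessments". The only separation it states is from assessments.
- Section 2.5 (Control Group) describes preparation differently: "Both drinks (240 mL each) will be prepared by a third‐party supplier to ensure consistency and double‐blinding".

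On blinding, section 2.13 says: "Blinding will be maintained for participants, assessors (care providers), and investigators". The independent staff member is not on that list.

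**The concern.** Allocation concealment requires that whoever enters the next participant does not know the next assignment. Sealed envelopes achieve this only if the enroller did not make or fill them. Here the same role generates the list, looks after the envelopes and enrols.

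Double-blinding also requires that nobody who knows the content of a drink deals with the participant in a way that could signal it. The primary outcome is maximal power in an all-out test, and RPE is self-rated. Both depend on effort and expectation. If the person providing the drink knows what it is, a cue could differ between a wrestler's beetroot visit and his placebo visit.

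**Working it through.** The plan gives no figure on this point, so the check is a comparison of the sections, followed by a short argument about where a bias could enter.

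**1. Who does what**

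| Task | Role named | Section |
|---|---|---|
| Propose candidates | Coaches | 2.2 |
| Apply eligibility criteria | Not named | 2.10 |
| Obtain consent | Principal investigator or trained staff | 2.11 |
| Generate the sequence | Independent staff member | 2.13.3 |
| Prepare the envelopes | An independent staff member | 2.13.2 |
| Manage the envelopes | An independent staff member | 2.13 |
| Label the drinks | Independent staff member | 2.13 |
| Enrol after screening | Independent staff member | 2.13.3 |
| Provide the drinks | Independent staff member | 2.13.3 |
| Give the drink at T = 0 h | Not named | 2.3 |
| Wingate tests, blood sampling, RPE | Assessors, stated as blinded | 2.13 |

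No section gives sequence generation or enrolment to anyone else. The web-based tool in 2.13 and 2.13.1 does not change this, because 2.13.3 has the staff member generate the sequence. The order of allocation for all 28 wrestlers is therefore known to the person who enrols them.

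**2. Where foreknowledge can act.** Write a wrestler's result as his own level *a* plus a treatment effect τ for beetroot and a period effect π (second visit minus first).

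- The within-person difference, beetroot minus placebo, is τ + π when placebo comes first and τ − π when beetroot comes first. The level *a* cancels, so steering stronger wrestlers into one sequence does not by itself shift the contrast.
- The sum of the two visits contains 2*a*. Comparisons between sequences, such as the sequence and carryover effects planned in 2.21, therefore rely on sequence groups formed at random, and steering would distort them.
- With n₁ completers starting on placebo and n₂ starting on beetroot, the mean difference is τ + π(n₁ − n₂)/(n₁ + n₂). With equal numbers (28 / 2 = 14 each) the π term is zero. Unequal dropout by sequence leaves part of it in the paired comparison.

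**3. Where unblinded contact can act.** Let the handover add a cue effect c_B at the beetroot visit and c_P at the placebo visit. The within-person difference then gains c_B − c_P, which does not cancel. It is zero on average if the person handing over the drink does not know its content. The document gives nothing from which to estimate it otherwise.

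**4. Extent.** Two visits for each of 28 wrestlers give 28 × 2 = 56 planned handovers, if 2.13.3 means that the staff member gives the drink in person each time.

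**5. Timing.** Section 2.3 puts the drink at T = 0 h, and baseline blood and anthropometry at T = 3 h. The upper-body test follows and then the lower-body test.

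**The case against.** The strongest reply is that the design already contains most of the harm, and much of it stands.

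- A reader might infer that the treatment comparison suffers selection bias as it would in a parallel-group trial. The document does not support that. Each completer receives both drinks, and 2.21 compares them within subject.
- A reader might infer that the staff member chooses who gets in. Coaches propose candidates, eligibility follows set criteria, and others obtain consent. What remains is possible influence on the order of entry, and so on which sequence a wrestler receives.
- A reader might infer that outcome assessment is unblinded. Section 2.13 says the reverse, and 2.13.2 keeps the staff member who prepares the envelopes out of assessments.
- A reader might picture cueing at the start of the test. The handover is 3 h earlier, which weakens that route without closing it.
- A reader might take it as stated fact that an unblinded person gives every dose. Section 2.3 does not say who gives the drink, and providing the drinks could mean supplying them to the visit team. Handing them over is the more natural reading.
- Sections 2.5 and 2.13 might be read as a flat contradiction about who prepares the drinks. They can be reconciled if the supplier manufactures both beverages and the staff member portions and labels them. The wording is ambiguous and needs reconciling, but it is not a proven conflict.

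None of this restores concealment from the enroller. Nor does any section say that the drink is handed over by someone without knowledge of the list.

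**Conclusion.** The point holds in this limited form. As written, allocation is not concealed from the person who enrols, and on the natural reading of 2.13.3 the drinks come from an unblinded person 3 h before effort-dependent tests. Foreknowledge threatens mainly the sequence and carryover terms and the balance of dropout between sequences. Unblinded contact at dosing is the only route of the two by which the within-person contrast could be affected directly, at up to 56 handovers. The size of either effect cannot be derived from the document.

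The conclusion assumes that the independent staff member in 2.13 and 2.13.3 is one and the same role, which is how the text reads. The part about dosing also assumes that providing the drinks means giving them to the wrestlers. The matter should be corrected, but it does not show that the main comparison is invalid.

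**What to change.** Separate the roles, using people whom the protocol already names.

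1. Whoever generates and holds the list neither enrols participants nor hands over drinks.
2. That person, or the third-party supplier if able to do so, codes the bottles by participant number and visit.
3. Consenting staff under 2.11, stated to have no access to the list, enrol each wrestler and hand over the next numbered bottle. Section 2.3 should name who gives the drink at T = 0 h.
4. Sections 2.5, 2.13, 2.13.2 and 2.13.3 are aligned. They should say who prepares the drinks, who labels them, and what purpose the envelopes still serve once the bottles are coded.

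The cost is a reassignment of existing tasks. The sample size (22, raised to 28), the endpoints and the analysis are unaffected. Section 2.1 states that recruitment had not begun at version 1.0, and 2.24 gives the route for an amendment. If recruitment has since started under the present wording, the report should state who enrolled the wrestlers and who handed over the drinks.

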### Safety

2.14

Although the occurrence of complications and adverse events linked to the intervention is considered improbable, participants will be prompted to self‐report any symptoms or adverse events they experience. The sole previously recorded side effects are beeturia (the appearance of red urine) and red stools [7, 38]. To ensure participant safety, the facilitator and a graduate student will be readily accessible by phone, allowing participants to promptly report any issues or inquiries. Any potential complications will be documented and addressed in consultation with a physician. Furthermore, communication and participant monitoring will be enhanced through the use of social networking platforms such as Telegram and WhatsApp.

